## 8. Safety indicators

The safety assessment will include the monitoring and recording of all adverse events (AEs) and serious adverse events (SAEs). Routine blood tests, blood biochemistry and vital signs as well as physical examination, ECG, and endometrium test will be performed regularly according to routine medical procedures.

## **9. Quality control and guarantee**

In order to further ensure the quality of clinical trials, a multi-center trial coordination committee is established to appoint the general director of clinical research and serve as the research coordinator among the clinical trial centers. The persons in charge of the research units and the persons in charge of the sponsors are members of the coordination committee. The Coordinating Committee is responsible for the implementation of the entire test and resolves issues related to the trial;

The sponsor will appoint the principal investigator to ensure that the rights of the subjects in the clinical trials are safeguarded, the data of the trial records and reports are accurate, complete and correct, and to supervise the implementation of clinical trial programs, the clinical trial management regulations and relevant laws and conduct regular on-site supervision visits to each center;

For eCRF forms that do not meet the program, have the right to ask the researcher who participates in clinical trials to re-enter them, but they must follow the authenticity of the information.

Through pre-clinical training, researchers are fully aware of and understand the clinical trial program and the specific contents of each indicator. For the objective indicators specified, inspections should be conducted according to the timing and methods prescribed by the program. Attention should be paid to the observation of adverse reactions or unexpected toxic side effects, and follow-up observations are performed.

## **10. The methods of observation, record and report of adverse events**

### **10.1 Adverse events**

The term of adverse events encompasses any clinical syndrome, symptom and syndrome that occurs in the subject and affects the health of the subject, or the appearance or worsening of a disease during the clinical study. The term also includes other clinically relevant conditions that occur in the laboratory and during the testing process, for example, unplanned measures of diagnosis and treatment, or resulting in withdrawal from the trial. Adverse events may be: new disease; worsening of symptoms or signs of treatment status, or worsening of the accompanying disease; not related to participating in the trial; a combination of one or more factors. Therefore, the term "adverse event" does not mean a causal relationship with the trial drug.

## 10.2 Serious adverse events

The following adverse events occur at any dose of trial drug or at any time during the observation period, including: leading to death; immediate life-threatening; need of hospitalization or prolonged hospital stay; disability; leading to congenital malformations; important medical significance (referring to those that do not immediately endanger life or cause death or need hospitalization, but may harm the patient or need to take steps to prevent one of the consequences defined above) requiring medical treatment to prevent permanent injury or damage.

## 10.3 Medical side effects

Harmful rather than expected reactions which has a causal relationship with the drug use is generated during the normal application of the drug at the prescribed dose. In clinical trials of a new drug or new use of a drug, when its therapeutic dose has not been determined, all adverse but not expected reactions that have a causal relationship with drug use should also be regarded as adverse drug reactions.

## 10.4 Severity of adverse reactions

Mild: can be tolerated by the patient, does not affect continued treatment, does not require special treatment, and has no effect on the rehabilitation of the patient.

Moderate: cannot be tolerated by the patient, and needs to be discontinued or given special treatment, and has a direct effect on the rehabilitation of the patient.

Severe: endangers the patient's life, disability or death, and immediate withdrawal or urgent treatment is required.

## 10.5 Judgment of causality between adverse reactions and drugs

### 10.5.1 Related indicators of causality judgment

- (1) Whether there is a reasonable sequential relationship between the time of starting drug use and the time when the suspected adverse reaction occurs.
- (2) Whether the suspicious adverse reaction meets the known adverse reaction type of the drug.
- (3) Whether the suspected adverse reactions can be explained by the patient's pathological condition, drug combination, combination therapy, and previously used therapy.
- (4) Whether the suspicious adverse reactions can be reduced or disappeared by withdrawal or reducing the dose.
- (5) Whether or not the same adverse drug reactions occur again after receiving the same drugs

Multi-center, Randomized, Double-blind, Controlled Study of the Effectiveness and Safety of Mifepristone in Treating Adenomyosis

again.

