### 4.3 Rationality of research design

In order to avoid selection bias or bias by any other investigators' or subjects' understanding of the treatment used, the trial design was performed according to the principles of randomization, allocation concealment, double-blind, placebo control. The placebo control is necessary because of the more pronounced placebo effect observed in literature studies.

Multi-center, Randomized, Double-blind, Controlled Study of the Effectiveness and Safety of Mifepristone in Treating Adenomyosis

From an ethical point of view, placebo-controlled trials are considered acceptable because they allow the patients in the study to receive analgesics other than research drugs (indomethacin suppositories), which have been passed by the ethics Committee of Women's Hospital, School of Medicine Zhejiang University.

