### 10.5.2 Causality judgment

Based on the above five indicators, the analysis of causality is divided into 5 levels of affirmative relevance, probable relevance, possible relevance, suspicious relevance, and impossible relevance.

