#### Causality judgment of adverse reactions

|                                                               | Affirmative
relevance | Probable
relevance | Possible
relevance | Suspicious
relevance | Impossible
relevance |
|---------------------------------------------------------------|----------------------------------|-------------------------------|-------------------------------|---------------------------------|---------------------------------|
| A reasonable time sequence with the trial drug                | +                                | +                             | +                             | +                               | -                               |
| Known types of adverse reactions of drug                      | +                                | +                             | +                             | -                               | -                               |
| Relief or disappear after drug withdrawal                     | +                                | +                             | ±                             | ±                               | -                               |
| Adverse reactions return or disappear after re-administration | +                                | ?                             | ?                             | ?                               | -                               |
| Cannot be explained by subject's disease                      | +                                | +                             | -                             | ±                               | -                               |

Note: (1) “+” means affirmation; “-” means disavowal; “±” means difficulty in affirming or denying; “?” means that the situation is not clear. (2) Affirmative relevance, probable relevance can be considered as adverse reactions caused by drugs.

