## 10.6 Adverse event handling

### 10.6.1 Record and report

The researcher should explain to the patient and ask the patient to truthfully reflect the changes in condition after medication. Physicians avoid suggestive questions.

While observing the efficacy, pay attention to observe adverse reactions or unexpected toxic side effects (including symptoms, signs, laboratory inspection). No matter whether the adverse reactions or adverse events are related to the trial drug, they should be recorded in detail, including the time of appearance of adverse reactions, symptoms, signs, degree, duration, laboratory test indicators, treatment methods and results, the course and follow-up time and so on. The details of the drug combination are recorded in order to analyze the correlation between adverse reactions and the trial drugs.

Multi-center, Randomized, Double-blind, Controlled Study of the Effectiveness and Safety of  
Mifepristone in Treating Adenomyosis

Records should be signed and dated. If there are serious adverse events during the trial, the researcher must report to the local provincial food and drug supervision and administration

department, the State Food and Drug Administration, the sponsor, the clinical research responsible unit and the medical ethics committee within 24 hours. Researchers should sign and date the report. It should be recorded when, in what way and to whom serious adverse events were reported in the source data. The sponsor should immediately notify the participating units and ensure to meet reporting procedures required by all laws and regulations.

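### The causality table narrows indicator (3) to the subject's disease, so a reaction due to another drug can be graded 'probable' if the other rows also fit

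*Protocol*

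**What the plan says.** Protocol 10.5.1 lists five indicators for judging causality. The third asks "Whether the suspected adverse reactions can be explained by the patient's pathological condition, drug combination, combination therapy, and previously used therapy", which gives four alternative explanations: the disease, concomitant drugs, concurrent therapy and earlier therapy.

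Section 10.5.2 then says: "Based on the above five indicators, the analysis of causality is divided into 5 levels". The table below it has five rows and five grades. The row that stands for indicator (3) reads "Cannot be explained by subject's disease". It is + for 'affirmative' and 'probable', - for 'possible' and 'impossible', and ± for 'suspicious'.

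Note (2) under the table says: "Affirmative relevance, probable relevance can be considered as adverse reactions caused by drugs". Section 10.6.1 adds: "The details of the drug combination are recorded in order to analyze the correlation between adverse reactions and the trial drugs". Section 15.5 (4) reports adverse events and adverse reactions, overall and by group.

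**The concern.** The table turns the indicators into a grade, and it drops three of the four alternative explanations in indicator (3). If an assessor works from the table alone, knowing that another drug caused the event does not change any row, so it cannot lower the grade.

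At stake is the by-group count of adverse reactions, which is how harm attributed to the drug is reported. Section 5 of the protocol names 16 hospitals. If some assessors follow the row and others go back to the indicator, the same event can receive different grades at different sites.

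**Working it through.** The protocol gives no figure to reproduce here. The check sets the indicators against the rows and then matches score patterns to columns.

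**Step 1: indicators against rows.**

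| Indicator (10.5.1) | Row in the table | Match |
|---|---|---|
| (1) time order | time order with the trial drug | yes |
| (2) known reaction type | "Known types of adverse reactions of drug" | yes |
| (3) disease, concomitant drugs, concurrent therapy, earlier therapy | "Cannot be explained by subject's disease" | disease only: 1 of 4 |
| (4) improves on stopping or lowering the dose | "Relief or disappear after drug withdrawal" | yes, dose reduction omitted |
| (5) recurs on re-exposure | effect of re-administration | yes |

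**Step 2: the columns as patterns.** The row order is time, known type, withdrawal, re-administration, not explained by disease.

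- Affirmative: + + + + +
- Probable: + + + ? +
- Possible: + + ± ? -
- Suspicious: + - ± ? ±
- Impossible: - - - - -

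**Step 3: a reaction due to another drug.** Adenomyosis does not explain it, so the last row is +. Let time and known type each be + or -, withdrawal be +, - or ±, and re-administration be +, - or ?. That gives 2 x 2 x 3 x 3 = 36 patterns of the other four rows.

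- Last row +: 2 of 36 match a column, + + + + + (affirmative) and + + + ? + (probable).
- Last row -: 2 of 36 match, + + ± ? - (possible) and - - - - - (impossible).
- Last row ±: 1 of 36 matches, + - ± ? ± (suspicious).

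Without re-administration, the reaction is therefore 'probable' only if time, known type and withdrawal are all +. If one of the three fails while the last row stays +, no column matches and the table gives no grade.

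**Step 4: the last row widened to all of indicator (3).** The same reaction now scores - in the last row. 'Affirmative' and 'probable' both need + there, so neither can apply. It matches 'possible' only when withdrawal is ±. With clear relief after withdrawal it scores + + + ? -, which matches no column. That gap exists today for an event explained by the disease.

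**Step 5: can a size be given?** The misattributed count in one arm would be 75 (the planned arm size) x share using the other drug x share of users with a reaction it causes x share of those also scoring + on time, known type and withdrawal x share graded from the row label alone. The documents give only the 75.

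**The case against.** The strongest reply is that the protocol already brings concomitant drugs into the grade. Section 10.5.2 rests the grade on all five indicators, so indicator (3) applies whole, and 10.6.1 has the drugs recorded for that use. The rows read as short labels: the withdrawal row also omits the dose reduction named in indicator (4). Note (2) is permissive. This stands in part: an assessor may still weigh another drug, so it would be wrong to say that the recorded data can never change a grade. But nothing says whether the indicator or the row governs when they differ.

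It is also true that the route to 'probable' is narrow. A reaction that clears when the analgesic stops while the trial drug continues gives no positive withdrawal result for the trial drug. Under 10.4 a mild reaction does not interrupt treatment, so it would normally give none either. This stands, and it limits the point to events that meet all three other conditions.

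Exposure is uncertain too. Section 4.3 supports the placebo arm by letting women receive indomethacin suppositories. Section 6.8 (1) lists non-steroidal anti-inflammatory drugs among the forbidden drugs and bars painkillers taken without a doctor's consent. Exclusion criterion (11) covers women who cannot stop such drugs. These passages must be reconciled, and until then the amount of analgesic use cannot be judged. The mismatch itself does not depend on it, because it applies to any concomitant drug or therapy.

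**Conclusion.** The point holds and is minor. The last row is narrower than the indicator it stands for. Read literally, the table lets a reaction due to another drug be graded 'probable', and counted as drug-caused, when time, known type and withdrawal are also +. Only the adverse-reaction count is exposed. Under 10.6.1 every adverse event is recorded whatever its relation to the drug, so the count of all adverse events by group does not depend on the grade. Section 15.5 treats the safety variables descriptively.

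Two stronger readings are tempting. A reader might infer that reactions to analgesics are generally graded 'probable'. The three other conditions, and the appeal to all five indicators in 10.5.2, rule that out.

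A reader might also infer that analgesics will be used more on placebo, since the sample-size section expects a week-12 VAS of 3.25 there against 2.01 on mifepristone, and that the drug will therefore look safer than it is. The documents do not support this. They give no analgesic use by arm, no rate of reactions to analgesics, and no frequency with which the trial drug is stopped, which could itself differ by arm. Neither size nor direction can be stated. Grading under the blind does not settle the matter either way, because it does not make the use of other drugs equal between arms.

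**What to change.** Reword the last row to cover the whole of indicator (3), for example: *Not explained by the subject's disease, concomitant drugs, other therapy or previous therapy*.

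Add one sentence under the table: an event that has such an explanation is graded no higher than 'possible', including when it resolves after withdrawal (+ + + ? -). The sentence is needed because rewording alone would leave that pattern without a grade.

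If the eCRF, which is not shown, repeats the row label, use the same wording there. The cost is one table row, one sentence and possibly one form label. No new data are needed, since concomitant drugs are already recorded at Interviews 3 to 6 (Table 7-1).

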### 10.5.2 Causality judgment

Based on the above five indicators, the analysis of causality is divided into 5 levels of affirmative relevance, probable relevance, possible relevance, suspicious relevance, and impossible relevance.

#### Causality judgment of adverse reactions

|                                                               | Affirmative
relevance | Probable
relevance | Possible
relevance | Suspicious
relevance | Impossible
relevance |
|---------------------------------------------------------------|----------------------------------|-------------------------------|-------------------------------|---------------------------------|---------------------------------|
| A reasonable time sequence with the trial drug                | +                                | +                             | +                             | +                               | -                               |
| Known types of adverse reactions of drug                      | +                                | +                             | +                             | -                               | -                               |
| Relief or disappear after drug withdrawal                     | +                                | +                             | ±                             | ±                               | -                               |
| Adverse reactions return or disappear after re-administration | +                                | ?                             | ?                             | ?                               | -                               |
| Cannot be explained by subject's disease                      | +                                | +                             | -                             | ±                               | -                               |

Note: (1) “+” means affirmation; “-” means disavowal; “±” means difficulty in affirming or denying; “?” means that the situation is not clear. (2) Affirmative relevance, probable relevance can be considered as adverse reactions caused by drugs.

## 10.6 Adverse event handling

### 10.6.1 Record and report

The researcher should explain to the patient and ask the patient to truthfully reflect the changes in condition after medication. Physicians avoid suggestive questions.

While observing the efficacy, pay attention to observe adverse reactions or unexpected toxic side effects (including symptoms, signs, laboratory inspection). No matter whether the adverse reactions or adverse events are related to the trial drug, they should be recorded in detail, including the time of appearance of adverse reactions, symptoms, signs, degree, duration, laboratory test indicators, treatment methods and results, the course and follow-up time and so on. The details of the drug combination are recorded in order to analyze the correlation between adverse reactions and the trial drugs.

Multi-center, Randomized, Double-blind, Controlled Study of the Effectiveness and Safety of  
Mifepristone in Treating Adenomyosis

Records should be signed and dated. If there are serious adverse events during the trial, the researcher must report to the local provincial food and drug supervision and administration

department, the State Food and Drug Administration, the sponsor, the clinical research responsible unit and the medical ethics committee within 24 hours. Researchers should sign and date the report. It should be recorded when, in what way and to whom serious adverse events were reported in the source data. The sponsor should immediately notify the participating units and ensure to meet reporting procedures required by all laws and regulations.

#### 10.6.2 The treatment of the subjects

When an adverse reaction is found, the researcher can take the necessary measures according to the condition. For example: adjusting the dosage of the trial drug, temporarily discontinuing the drug, permanently discontinuing the drug, taking the accompanying drug, and so on. In the event of a serious adverse event, the unit that undertakes the clinical trial must immediately take necessary measures to protect the safety of the subject. All adverse events should be tracked and the details of the treatment process and results should be recorded until they are properly resolved or the condition is stable. If abnormalities are detected, they should be traced back to normal.

Hospital, outpatient, home visits, telephone, communications and other forms of follow-up methods can be selected according to the severity of adverse reactions.

## 11. Study medical records, eCRF filling and transfer

Each case in group must complete the medical record and electronic case report form, which filled in by the researcher and inspected by the chief research officer before data entry and management.

## 12. The relevant requirements of observation, record and summary

- (1) Cases involved in this clinical trial are required to sign patient informed consent.
- (2) Carefully observe, record and fill in the electronic case report form according to the program and observation form. The electronic case report form must not be absent.
- (3) Carefully record the subject's medication and record in detail the reasons for not using the medication as prescribed.

Multi-center, Randomized, Double-blind, Controlled Study of the Effectiveness and Safety of Mifepristone in Treating Adenomyosis

- (4) The research medical record and electronic case report form shall not be arbitrarily modified. If there is a need for change, the researcher shall sign and date at the amendment department (the electronic case report form will be automatically recorded).
- (5) The study medical record of outpatient cases should be affixed with the original laboratory examination report form, while the study medical record of hospitalized case should be affixed with a copy of the laboratory examination report form.
- (6) After the observation is over, all electronic case report forms are reviewed by the leaders of each participating organization and uploaded to the EDC. The original medical record is preserved by the recode department of each participating organization.
- (7) Clinical trial statistics organization perform the statistical analysis with all cases of each trial center, and provided the statistical results to the participating organizations to write the “Clinical Trial Summary”. Finally, the responsible institution should complete the "Clinical Trial Summary Report”.

